#### Sociodemographic and Basic Medical Data

To establish intergroup homogeneity, the following data will be collected from the patient’s medical history: age, primary diagnosis at the time of admission, triage classification (3 to 5), and the presence of a caregiver or companion at the time of admission to the emergency room.

#### Participant Timeline

Details of the participant timeline are listed in Figure 1.

**Figure 1 figure1:**
[figure not shown]
Participant timeline. EMT: Environmental Music Therapy.

### Intervention Protocol

#### Environmental Music Therapy: Intervention Group 1

Environmental Music Therapy is a music therapy technique that uses live music to modulate the potentially stressful effects of the environment toward an atmosphere that provides a sense of comfort and security. For this study, the intervention was adapted based on the 4 steps of EMT described by Rossetti [36]: assessment of the environment, initiation of the intervention, development of the intervention, and closure.

Evaluation of the environment: Before starting the intervention, the music therapist will observe the emergency waiting room for a couple of minutes to be aware of the number of people present and the content, volume, or timbre of the current auditory environment. In addition, it will be detected if, for example, someone shows signs of acute pain or signs of restlessness or anxiety. Assessing the environment also includes finding an optimal place for the music to be heard evenly throughout the room, without disturbing the movements and flow of patients, caregivers, and staff.Beginning of the intervention: Before starting EMT, the music therapist will introduce him or herself to the patients and caregivers present and explain the role and purpose of the music. Patients and caregivers will be informed that they can participate in listening to the music in every way that feels comfortable for them, for example by just continuing what they are currently doing, by breathing slowly with the music, or by imagining themselves being in a safe place.Development of the intervention: The instruments used will be an acoustic guitar (Yamaha C-40), an ocean drum (a drum with a double skin on which small metal balls roll imitating the sound of the waves), and a Samafon (an instrument consisting of aluminum tubes of different sizes that are struck with a soft mallet producing long-lasting single or combined tones). The different instruments and timbres will be introduced gradually. The music will consist of improvised instrumental music at a slow to moderate tempo, using free-flowing melodies, and simple chord progressions, focusing on creating moments of tension and resolution. The music therapist will also use his or her voice to accompany the music but without any lyrics or words. While the musical characteristics are aimed to remain consistent during the intervention, their selection, order, and content, will be adapted according to a constant re-evaluation of the environment.Closing: after 20 minutes, the music therapist will gradually decrease the volume until the music stops.

#### Prerecorded Music: Intervention Group 2

The prerecorded music will consist of a recording including the same musical features and musical instruments as the live music. The recording will be made by the same music therapists who will perform the EMT intervention. To playback the music, a Bluetooth speaker (JBL Go 3) will be placed centrally in the ED waiting room and handled by the music therapists. The recorded music will last 20 minutes and the music therapists will remain present at the waiting room but will not engage in any further activities.

#### Standard Care Only: Control Group

The control group will receive standard care in the emergency room waiting room as provided by each hospital, but without being exposed to EMT or prerecorded music. However, the music therapist will remain present in the waiting room but will not engage in any activities. The control condition will last for 20 minutes.

### Data Collection and Storage

The data will be collected by a research assistant in each hospital and stored in a REDCap (Research Electronic Data Capture; Vanderbilt University) database to maintain confidentiality and data safety. During the data collection process, the database will be audited to identify the presence of inconsistent or atypical data. At the end of the data collection, a random selection of the data of 10% of the participants will be made to verify the paper version of the questionnaires against the electronic database.

### Potential Harms and Adverse Events

Any potential harm or adverse events related to the intervention will be recorded and communicated to the ethics committee according to the hospital site’s guidelines.

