#### Participant Selection and Randomization

Selection of the participants will be made by convenience sampling. The intervention and control conditions will take place on the same day of the week (Tuesdays, Thursdays, and Fridays) and at the same hour (11 to 11:30 AM) at both hospitals. The order of the 3 conditions (EMT, prerecorded, control) will be randomized by days of intervention. For this, a block size randomization of multiples of 3 will be used, ensuring an equal number of interventions for each arm of the study. Intervention A will be established as EMT, intervention B as prerecorded music, and intervention C as standard care.

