#### Blinding

Due to the nature of the interventions, music therapists, patients, caregivers, and data collectors, will not be blinded. Data analysis will be carried out by a member of the research team blinded to the result of the randomization.

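### Adverse events are recorded according to an unblinded judgement that they are related to the intervention, so recorded counts are not comparable between the three arms

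*Protocol article*

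**What the plan says.** The section Potential Harms and Adverse Events is one sentence: "Any potential harm or adverse events related to the intervention will be recorded and communicated to the ethics committee according to the hospital site’s guidelines". It names no assessor and no criteria for relatedness, and does not say how the rule applies in each arm.

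Other sections bear on how that sentence works:

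- **Blinding:** "music therapists, patients, caregivers, and data collectors, will not be blinded". Only the data analyst is blinded.
- **Study Design:** two intervention groups are set against a control group. The control section describes that group as being in the waiting room "without being exposed to EMT or prerecorded music".
- **Participant Selection and Randomization:** "Intervention A will be established as EMT, intervention B as prerecorded music, and intervention C as standard care".
- **Data Collection and Storage:** a research assistant at each hospital collects the data, with no difference by arm.
- **Data Analysis and Potential Limitations:** only people with both a baseline and a post form are analysed. The distribution of those without a post form is to be compared between groups.

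**The concern.** People waiting in an emergency department in pain or anxiety will sometimes become distressed, complain or walk out under any condition. To tell whether music changes how often this happens, events must be counted on the same basis with and without music. A rule that admits an event only after someone who knows the condition has linked it to the intervention does not give that. It could produce an apparent excess under music, because only there is music available as a cause. It could also hide a real excess, because events are put down to the illness. A later statement that there were no harms, or more harms, with music would then rest on attribution and not on observed frequency.

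**Working it through.** The plan gives no harm rate, harms hypothesis or harms sample size, so there is no figure to reproduce. The check is a comparison of sections, followed by an illustration with assumed rates.

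**1. Where the filter sits.** The harms sentence attaches relatedness to what is recorded, not to a classification made after recording. By the Blinding section, everyone present who could apply it knows the day's condition.

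**2. What the intervention refers to.** Usage in the article is mixed.

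- *Reading A, music only.* Study Design separates intervention groups from a control group, the randomization section contrasts intervention and control conditions, and the harms sentence uses the singular. This is the natural reading. Control events then do not qualify.
- *Reading B, all three conditions.* The randomization section labels standard care as intervention C, and the outcome sections apply the scales before and after each intervention in every arm. Control events then qualify if related to standard care, EMT events if related to live music, and prerecorded-arm events if related to the recording. The three counts answer three different questions.

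Neither reading gives counts that can be set side by side.

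**3. Whether the scales cover the gap.** Anxiety, stress, well-being and (in patients) pain are self-rated before and after every condition, so worsening can be compared among completers. Someone who leaves because of distress or annoyance has no post score and drops out of the analysis. The planned check on missing post forms compares their distribution between groups but mentions no reasons. It therefore would not separate a person called for treatment from one who left because of the session.

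**4. Size of the attribution effect (assumed rates).** Input from Sample Size: 82 patients and 49 caregivers per arm, so 82 + 49 = 131 people per arm.

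- Assume 5% of patients have an untoward event in every arm: 0.05 × 82 = 4.1 per arm. If 40%, 20% and 0% are judged related in the EMT, prerecorded and control arms, the recorded counts are 4.1 × 0.4 = 1.6, 4.1 × 0.2 = 0.8 and 0. The true difference is nil.
- Assume 3% of all participants: 0.03 × 131 = 3.9 per arm. The recorded count can lie anywhere from 0 to 3.9, depending on attribution alone.

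**5. What a zero would mean.** If all events were recorded, zero in n people gives a one-sided 95% upper bound of 1 − 0.05^(1/n): 3.6% for n = 82, 5.9% for n = 49 and 2.3% (0.0226) for n = 131. This treats people as independent and ignores assignment by day. If only a fraction q of events is judged related, a recorded zero bounds the all-cause rate at about 0.0226/q. That is 5.65% at q = 0.4 and 11.3% at q = 0.2. Since q is unknown, the zero supports no usable bound.

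**6. Detection.** Under EMT the therapist first observes the room, when "it will be detected if, for example, someone shows signs of acute pain or signs of restlessness or anxiety", and the music "will be adapted according to a constant re-evaluation of the environment". In the prerecorded arm "the music therapists will remain present at the waiting room but will not engage in any further activities", and the control section says much the same. This is a difference in activity. The article presents the observation as a step of the EMT technique, however, and does not link it to any harms record.

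**The case against.** **The wording is looser than a strict filter.** The sentence does not say that only related events are recorded, and the qualifier could be read as attaching to adverse events but not to potential harm. That is possible, but the sentence then has two categories with different rules and no line between them, so it still needs clarifying.

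**A reader might infer that the control count is zero by construction.** The documents do not establish this. It follows under reading A, which is the more natural one, but the intervention C label leaves reading B open.

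**A reader might also infer that harms are detected unequally because only the EMT therapist watches the room.** This is not shown. Research assistants collect data in every arm, and Potential Limitations says that therapists do not interfere with recruitment or data collection. Unequal detection remains a possible risk, and the point does not depend on it.

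**Nor is it right that harms cannot be compared at all.** Worsening on the scales can be compared among completers. The problem is confined to recorded events and to people without a post form.

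**The article is a condensed source.** It defers to hospital guidelines that are not shown, and detailed ascertainment may sit in a fuller protocol. The absence of such detail is no fault. But the relatedness condition is a stated rule. If a fuller document records all events, the article misdescribes it.

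**No between-arm harms test is planned**, and the exposure is 20 minutes of music. Both are true, and they keep the point small.

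**Conclusion.** The point holds in a limited form. As written, the recording of adverse events depends on a relatedness judgement open to people who know the condition, and under either meaning of the intervention the recorded counts are not comparable between arms. The scales do not repair this for people who leave early.

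The conclusion rests on reading the relatedness qualifier as a condition for recording, which is the natural reading though not the only possible one. The sizes in the illustration rest on assumed event rates of 3% or 5% and assumed attribution fractions. They show that attribution alone can create a difference, not that it has. No stated efficacy analysis is affected. In a low-risk trial this is a minor point, but it bears directly on any safety statement in the final report.

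**What to change.** **Rewording.** Change the harms sentence so that the research assistant records untoward events between the baseline and post forms in the same way in all three conditions, regardless of presumed relation. Examples are distress, a complaint, a request to stop the music, or leaving because of the session. Relatedness is judged afterwards, and counts are reported by arm.

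**Who records.** This should be the research assistant. Giving the therapist an observation task in the prerecorded and control conditions would conflict with the therapist's stated inactivity there and with keeping therapists out of data collection. It would also carry an element of EMT into the comparators.

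**Sessions already held.** By November 2024, 216 of 246 patients (87.8%) and 134 of 147 caregivers (91.2%) had been enrolled. Against the targets, that left 30 patients and 13 caregivers to whom a new rule could apply from then on, and results were expected by May 2025. Most of the remedy therefore lies in reporting: state how events were collected and, if only related events were logged, draw no between-arm safety conclusion.

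**Cost.** A few lines on the session form and in REDCap, plus a short amendment if any sessions remain. No extra staff are needed. The downside is that some emergency department events unrelated to the sessions will be logged.

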### Data Analysis

Regarding the sociodemographic and medical data, a descriptive analysis will be carried out. For continuous variables and according to the nature of the data, measures of central tendency and interquartile range or mean and SD will be used, and evaluated with the Shapiro-Wilk test. Categorical variables will be analyzed and summarized using frequencies. Association tests of categorical variables will be evaluated using the chi-square statistic or Fisher exact test in the case of tables with cells with expected values less than 5. For the comparison of measures of central tendency in the cases of quantitative variables, tests such as the Student *t* test or sum of Wilcoxon or Kruskal–Wallis ranges will be performed, depending on the presence or not of normality in the distribution of the variables. A statistical significance value of 5% will be used for all hypothesis test cases.

The analysis regarding the effect of the interventions will be carried out separately by type of participant (patient or caregiver). The effect on state anxiety, stress, pain (only patients), and well-being will be evaluated using 3×2 factorial ANOVA. Then a post hoc analysis will be performed using the Student *t* test and Bonferroni adjustment. A multiple linear regression analysis will be carried out to evaluate the variables (state anxiety, age, sex, type of participant, waiting time, and reason for consultation) that modify the effect of the interventions on the state anxiety, stress, pain, and well-being levels. Only data from patients and caregivers who will complete both baseline and postintervention questionnaires will be analyzed. However, to avoid bias we will assess if the distribution of participants who did not fill out the postintervention questionnaires is similar among the groups.

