#### Sample Size

The sample size was calculated based on the primary outcome of this study using G*Power 3.1.9.7 (Heinrich Heine University Düsseldorf) [25] and considering that the study design corresponds to a 3×2 factorial design (3 groups and 2 repeated measures). Therefore, we will determine the effect of treatment between the groups using a 2-way ANOVA and repeated measures. We chose a statistical power of .80, a significance level of .05, and an effect size of =.01, the effect size was determined based on previous research [22] and the expected magnitude of differences between groups. The sample size calculation resulted in 246 participating patients, distributed in 82 per group.

In addition, a separate sample size calculation was performed for participating caregivers, following the same procedure as described for the patients and considering an effect size of η^2^=.017, resulting in 147 caregivers (49 per group). Both sample sizes are within the range reported in previous studies [22].

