#### Primary Outcome Measure

The primary outcome measure is state anxiety, measured with the Spanish version of the 6-item State-Trait Anxiety Inventory (STAI-6). In its original version, the STAI consists of 40 items, of which 20 measure trait anxiety and 20 items measure state anxiety [26]. The STAI-6 is a short version of the state scale and consists of 6 items evaluated on a 4-item Likert scale. The STAI-6 was validated in its original English version by Chlan et al [27], and its Spanish version by Perpiñá-Galvañ et al [28,29], and has been successfully used in a previous study on EMT in radiotherapy waiting rooms [22]. The STAI-6 will be applied before and after each intervention.

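### The planned 3×2 pre-post ANOVA is valid but is a change-score comparison; adjusting for baseline would be more efficient on data already collected

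*Protocol article*

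**What the plan says.** The Data Analysis section fixes the main test for the primary and all secondary outcomes: "The effect on state anxiety, stress, pain (only patients), and well-being will be evaluated using 3×2 factorial ANOVA". It names no tested term and no baseline covariate. Post hoc t tests with Bonferroni adjustment follow.

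The Sample Size section explains the label: "the study design corresponds to a 3×2 factorial design (3 groups and 2 repeated measures"), and adds that "we will determine the effect of treatment between the groups using a 2-way ANOVA and repeated measures". The planning inputs for patients are "We chose a statistical power of .80, a significance level of .05, and an effect size of =.01" (the effect-size symbol is missing from the text at hand), giving 246. For caregivers the calculation is described as "considering an effect size of η^2^=.017, resulting in 147 caregivers (49 per group").

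Baseline is available for the primary outcome: "The STAI-6 will be applied before and after each intervention". The Secondary Outcome Measures section says the same of the stress, pain and well-being scales. The analysis set is limited to completers: "Only data from patients and caregivers who will complete both baseline and postintervention questionnaires will be analyzed". Everyone analysed should therefore have a baseline score.

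A multiple linear regression in Data Analysis includes state anxiety among its variables, but it examines effect modification and is not the main comparison of arms.

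**The concern.** In a three-arm, two-time-point repeated-measures ANOVA, the treatment effect is carried by the group-by-time interaction. That F statistic is algebraically identical to a one-way ANOVA on post minus pre. A change score uses the baseline with its slope fixed at 1, whereas ANCOVA estimates the slope. When the pre-post correlation is below 1 and the variances are similar, the fixed slope over-corrects and adds noise.

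What is at stake is precision on the primary outcome. There is also a matter of chance imbalance. Whole days are assigned to a condition, so mean baseline anxiety can differ between arms by chance. A change score passes part of that imbalance into the estimate through regression to the mean, and ANCOVA does so less.

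**Working it through.** **Inputs.** From Sample Size: k = 3 groups, m = 2 measures, α = .05, target power .80, effect sizes .01 (patients, read as η² as for caregivers) and .017 (caregivers), N = 246 and 147. Assumed: pre-post correlation ρ (not stated), equal pre and post variance σ², independent participants.

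**Step 1: reproduce the plan's figures.** For the group-by-time interaction,

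λ = f²·N·m/(1−ρ), df₁ = (k−1)(m−1) = 2, df₂ = (N−k)(m−1) = N−3.

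With ρ = .5 and the stated effect sizes used as f²:

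- Patients: λ = .01 × 246 × 2/.5 = 9.84, df₂ = 243, power .804. The smallest N, in multiples of three, that reaches .80 is 246.
- Caregivers: λ = .017 × 147 × 2/.5 = 9.996, df₂ = 144, power .807. The smallest such N is 147.

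Both stated sizes reproduce exactly. Using f² = η²/(1−η²) instead gives 243 and 144, which is close. The between-groups main effect would need 726 and 429, and the time main effect 201 and 120. The plan was therefore sized on the paired interaction.

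**Step 2: compare variances.**

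- Change score: 2σ²(1−ρ)
- ANCOVA residual: σ²(1−ρ²) = σ²(1−ρ)(1+ρ)
- Ratio: (1+ρ)/2, which is below 1 for any ρ < 1

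At ρ = .5 the ratio is .75, so the gain is worth 1/.75 = 1.33 times the participants.

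**Step 3: power with the same treatment effect.** ANCOVA has λ = 4f²N/(1−ρ²) and df₂ = N−4. At ρ = .5 this is 4 × .01 × 246/.75 = 13.12 for patients and 4 × .017 × 147/.75 = 13.33 for caregivers.

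| ρ | Patients: change → ANCOVA | Caregivers: change → ANCOVA |
|---|---|---|
| .3 | .65 → .84 | .66 → .84 |
| .5 | .804 → .907 | .807 → .909 |
| .7 | .96 → .98 | .96 → .98 |
| .8 | .996 → .998 | .996 → .998 |

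At ρ = .5, ANCOVA would reach 80% power with 186 patients or 111 caregivers. A simulation with 10,000 runs per setting, using f² = η²/(1−η²), agreed (patients at ρ = .5: .809 and .906).

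**Step 4: separate the role of ρ from that of the effect size.** In the table, a higher ρ also lifts change-score power towards 1, which hides the gain. If change-score power is instead held at the plan's 80% (λ = 9.84), ANCOVA power for 246 patients is .943, .907, .867 and .846 at ρ = .3, .5, .7 and .8. The gain runs from about 14 points down to about 4.

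**Step 5: day-level randomization.** No day-level correlation or daily number is given. As an illustration, assume 8 patients a day (246/8 ≈ 31 days, so df₂ ≈ 31 − 3 = 28), a design effect of 1 + 7·ICC applied to λ for both analyses, and ρ = .5. Change-score and ANCOVA power are then about .70 and .83 at ICC .02, .62 and .76 at .05, and .52 and .65 at .10. Absolute power falls under both analyses and the advantage of ANCOVA remains.

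**The case against.** The strongest reply is that nothing here is an error. A change-score test keeps its type I error, uses the baseline, and under the planning assumptions meets the stated 80% power. This stands, so the point concerns efficiency only, and it would be wrong to say that the plan wastes the baseline.

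A reader might infer more from the Data Analysis wording, which omits repeated measures: that six cells of independent observations will be analysed and the pairing lost. The documents do not support that. Sample Size defines the label as including two repeated measures, and the stated N reproduces with pairing. A reader might also infer from the phrase about an effect between the groups that the group main effect, diluted by the pre-intervention score, is the test. The sizes of 726 and 429 that this would need show that the plan was not built on it. What remains is that the tested term is not named.

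Three limits also stand:

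- **ρ is unknown.** Pre and post are separated by a session of about 20 minutes, so a high ρ is plausible, and the gain is smaller there.
- **The headline powers assume independence**, which day-level randomization puts in doubt.
- **Timing of baseline.** The envelope is opened 10 minutes before the session and data collectors are unblinded. If knowledge of the condition affected who took part or how they scored at baseline, change-score and ANCOVA estimates would answer different questions, and neither would automatically be right. The timeline figure is not shown, so the order cannot be checked.

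**Conclusion.** The point holds as a recommendation on efficiency. The planned main test is a valid, unadjusted comparison of change scores, and baseline adjustment is more precise for any ρ below 1. At the ρ = .5 that reproduces the stated sample sizes, the gain is about 10 percentage points of power in both populations. It is about 19 points for patients at ρ = .3 and about 2 at ρ = .7 if the treatment effect is held fixed. These figures rest on an unstated correlation, equal pre and post variances, an effect size read as f² ≈ η², and independent participants. They do not show that the stated sample sizes are miscalculated, and ANCOVA does not by itself deal with clustering by day.

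**What to change.** Make the primary analysis the post-intervention STAI-6 compared between arms with baseline STAI-6 as covariate, in a model that accounts for the randomized day, fitted separately for patients and caregivers. Use the same form, each with its own baseline, for VAS-S, VAS-P (patients only) and each WB-NRS scale. Report the three pairwise adjusted mean differences with confidence intervals, keeping the planned Bonferroni adjustment. State that baseline questionnaires are completed before the condition is known, or describe the order actually followed.

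The covariate costs one error degree of freedom and needs no new data. The article reports 216 patients and 134 caregivers already enrolled at submission, so the wording should be fixed before the blinded analyst sees outcome comparisons.

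### Bonferroni-adjusted post hoc t tests are valid but less powerful than a three-arm trial needs; a closed test, or Holm if there is no gate, loses less

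*Protocol article*

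**What the plan says.** The Data Analysis section of the protocol article evaluates each outcome with a 3×2 ANOVA, separately for patients and caregivers. It continues: "Then a post hoc analysis will be performed using the Student" *t* "test and Bonferroni adjustment". The general level is set by "A statistical significance value of 5% will be used for all hypothesis test cases".

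The section is silent on two things that matter here: whether a non-significant ANOVA stops the post hoc step, and over how many comparisons the Bonferroni divisor is taken.

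The Sample Size section powers the ANOVA only, on the basis that "the study design corresponds to a 3×2 factorial design (3 groups and 2 repeated measures"). For patients: "We chose a statistical power of .80, a significance level of .05, and an effect size of =.01", and "The sample size calculation resulted in 246 participating patients, distributed in 82 per group". For caregivers: "considering an effect size of η^2^=.017, resulting in 147 caregivers (49 per group"). No power is given for any pair of arms.

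**The concern.** The trial's questions are pairwise. The closing paragraph of the Introduction sets live music therapy, recorded music and standard care against one another, and the Discussion presents live versus recorded music as a comparison not previously studied in this setting. The post hoc rule therefore decides whether a significant overall result becomes a statement about a named arm.

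With three arms, the only hypothesis above the three single pairs is that all arms are equal. Testing that at 5% and then each pair at an unadjusted 5% is a closed procedure, and it controls the familywise error strongly at 5% for that outcome and participant type. After a significant omnibus test it rejects every pair that Bonferroni rejects, and sometimes more. At stake is lost power for the comparisons the trial was set up to make, when enrolment was already at 216 of 246 patients and 134 of 147 caregivers at submission.

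**Working it through.** **Inputs.** From the Sample Size section: power .80, α = .05, three groups, two measurements, 82 patients and 49 caregivers per arm, effect sizes .01 and η² = .017. The symbol before .01 is lost in the text; I read it as η², as for caregivers. Assumptions: pre-post correlation ρ = .5 (not stated), three pairwise comparisons (not stated), two-sided tests, independent participants.

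**1. Reproduce the stated sample sizes.** For the group-by-time interaction, λ = N f² m/(1 − ρ), with m = 2 and 2 and N − 3 degrees of freedom.
- Patients, f = .10: λ = 246 × .01 × 2/.5 = 9.84, power .804. At N = 243 power is .798, so 246 is the smallest balanced N.
- Caregivers, f = .13: λ = 147 × .0169 × 2/.5 = 9.94, power .804. At N = 144 it is .795, so 147 is the smallest balanced N.

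Both figures reproduce exactly, which supports ρ = .5. With unrounded f² = η²/(1 − η²), λ is 9.94 for patients and 10.17 for caregivers, with power .808 and .814.

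**2. From the omnibus to a pair.** For change scores, λ = n Σ(μᵢ − μ̄)²/σ², and a pairwise contrast has squared noncentrality n(μᵢ − μⱼ)²/(2σ²).
- One arm differs by δ: Σ = (2/3)δ², so each true pair has .75λ.
- Even spacing by d: Σ = 2d², so an adjacent pair has .25λ and the extreme pair has λ.

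For patients (λ = 9.94) the noncentralities are √7.455 = 2.73, √2.485 = 1.58 and √9.94 = 3.15. Bonferroni tests at .05/3 = .0167. With 162 degrees of freedom this gives .623, .203 and .768. With λ = 9.84 it gives .617, .201 and .763.

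**3. Compare the rules (patients; Holm and closed test by simulation).**

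| Pattern and pair | Bonferroni | Holm | Closed test |
|---|---|---|---|
| One arm differs, each true pair | .62 | .65 | .73 |
| Even spacing, adjacent pair | .20 | .26 | .34 |
| Even spacing, extreme pair | .77 | .77 | .80 |

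Requiring a significant F before Bonferroni changes its column by at most about .01 (extreme pair .76). For caregivers, Bonferroni against the closed test is .63 v .73, .21 v .34 and .77 v .81.

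**4. Familywise error, independent participants.** All arms equal: Bonferroni .043, closed .050. Two arms equal and one different: Bonferroni .017, closed .049 to .050.

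**5. Size in participants.** To match the closed test, Bonferroni would need about 102 per arm instead of 82 (102/82 = 1.24) when one arm differs, and about 132 (132/82 = 1.61) for the adjacent pair.

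**6. Sensitivity.** Bonferroni power (one arm differs / adjacent pair) is .46/.14 at ρ = .3 and .86/.35 at ρ = .7. If the divisor covered all 15 pairs of the six cells, it would be .41/.08 at ρ = .5.

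**7. Clustering.** The Participant Selection and Randomization section randomises conditions by day. Assuming 4 patients per session and an intraclass correlation of .05 for change (neither is in the document), an ANOVA that ignores sessions has familywise error of about 7% with the closed test and about 6.5% with Bonferroni when all arms are equal. When two arms are equal it is about 6.5% against about 2.5%.

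**The case against.** Bonferroni after an ANOVA is valid and common, and it yields simultaneous intervals that agree with the decisions. That stands: a reader might infer an error-control fault, and there is none.

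A reader might also infer that the adjustment is redundant because the ANOVA already gates the pairwise tests. The article does not support this. It gives an order of steps, not a condition. Without a gate, three unadjusted tests would not hold 5%, so some adjustment is needed, and the gain available from Holm is smaller (.65 v .62; .26 v .20).

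Nor does Bonferroni account for most of the .20. An adjacent pair under even spacing is a small difference, and the closed test itself reaches only .34. For the extreme pair the gain is only 3 to 4 points.

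On clustering, the slack in Bonferroni happens to keep the error below 5% in the two-equal-arms case above. That is no remedy, since with all arms equal both rules exceed 5%. It does mean that the closed test cannot be said to hold 5% under a model that ignores sessions.

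Finally, relaxing a published rule late invites a charge of loosening it after the fact. That also stands, and makes timing a condition of the fix.

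**Conclusion.** The planned post hoc rule is a loss of efficiency. For patients the closed test gains about 11 points of power when one arm differs from the other two, 14 points for an adjacent pair under even spacing, and 3 to 4 points for the extreme pair. The absolute figures rest on three comparisons, a pre-post correlation of .5 and independent participants. The ordering is less fragile: whatever the correlation, the closed test rejects every pair that Bonferroni rejects after a significant F, and Holm always rejects at least what Bonferroni rejects. The 5% familywise error of the closed test depends on gating with the group-by-time interaction and on a model that respects randomisation by day. This is a worthwhile, inexpensive improvement and not a correction of an invalid analysis.

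**What to change.** Replace the post hoc sentence in the Data Analysis section with wording such as: If the group-by-time interaction (or the equivalent arm effect on change) is significant at 5%, the three pairwise contrasts from the same model are each tested at 5%; otherwise no pairwise claim is made. If no gate is wanted, replace Bonferroni with Holm and state that it covers the three pairs of arms. In either case the model must account for randomisation by day.

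The change should be documented and dated before the analyst is unblinded; the article does not show whether that point has passed. It needs no further recruitment. The cost is that neither the closed test nor Holm gives simple simultaneous confidence intervals that match the decisions. Bonferroni intervals can still be shown, with a note that one may include zero for a pair declared different.
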